| 8.4.1. Primary Analysis | 24 |
| 8.4.2. Exploratory Analysis | 24 |
| 8.5. Sample Size | 24 |
| 9 RESPONSIBILITIES | 25 |
| 9.1. Investigator Responsibilities | 25 |
| 9.1.1. Good Clinical Practice | 25 |
| 9.1.2. Institutional Review Board (IRB) Approval | 25 |
| 9.1.3. Informed Consent | 25 |
| 9.1.4 Confidentiality | 26 |
| 9.1.5. Study Files and Retention of Records | 26 |
| 9.1.6. Case Report Forms (CRFs) | 26 |
| 9.1.7. Protocol Compliance | 27 |
| 9.1.8. Study Discontinuation | 27 |
| 11 APPENDICES | 28 |
| Appendix 1. Study Procedures Table | 29 |
| 12 REFERENCES | 30 |

PROTOCOL SYNOPSIS

San Francisco Department of Public Health

[name]

San Francisco CA 94102

| Study Title: | Repeated-dose Brief Intervention to Reduce Overdose and Risk Behaviors among Naloxone Recipients |
| --- | --- |
| IND Number: | N/A |
| Study Center(s) Planned: | 1 site in the United States |
| Number of Subjects Planned: | At least 60 subjects (60 who inject drugs, with up to 10 additional non-injecting subjects) |
| Target Population: | Opioid-dependent naloxone recipient adults who have overdosed |
| Duration of Treatment: | Subjects will be enrolled in trial for 16 months |
| Objectives: | The primary objectives of this study are as follows:   1. To determine the feasibility of a randomized trial with REBOOT. 2. To determine acceptability of REBOOT. 3. To evaluate the influence of egocentric social network characteristics on overdose events and naloxone use.   The exploratory objectives of this study are as follows:   1. Preliminary efficacy estimates of REBOOT in decreasing overdose events (non-fatal or death), decreasing frequency of modifiable overdose / drug-related HIV risk behaviors, and increasing days of abstinence from illicit opioids and in substance use treatment. 2. Treatment effects on modifiable overdose risk behaviors. To provide a preliminary estimate of the effect of REBOOT, compared to TAU, on overdose risk behaviors, as measured by frequency of using opioids with alcohol, cocaine, or benzodiazepines (the most common modifiable overdose risk behavior), we will use GEE Poisson models with robust standard errors to assess reductions in overdose risks and linear mixed models to assess effects on the RAB scale. 3. Treatment effects on HIV risk behaviors. To provide a preliminary estimate of the effect of REBOOT, compared to TAU, on HIV risk behaviors among high-risk opioid users who have received take-home naloxone, as measured by frequency of using opioids with alcohol, cocaine, or benzodiazepines (the most common modifiable overdose risk behavior); and the HIV Risk Assessment Battery (RAB) drug-related risk scale score over 16 months. We will use GEE Poisson models with robust standard errors to assess reductions in overdose risks and linear mixed models to assess effects on the RAB scale. 4. Treatment effects on discontinuation of opioid use. We will use GEE Poisson models with robust standard errors to assess evidence that the intervention increases days of abstinence from illicit opioids and days of drug treatment within each of five 4-month reporting periods. 5. Treatment effects on management of witnessed overdose*.* We will use GEE Poisson models with robust standard errors to assess evidence that the intervention increases the use of naloxone during overdose events witnessed by participants. 6. Prospective evaluation of naloxone recipients. Given the apparent effectiveness of naloxone alone in reducing overdose mortality, we will analyze all measures to generate descriptive data from the control arm. These include trajectories in self-reported drug use, baseline prevalence and incidence of HIV and HCV, longitudinal records on receipt of naloxone refills, and trends in utilization of EMS after naloxone administration (a potential cost savings of overdose prevention to be explored in future mathematical modeling efforts). Although sample size is small, results will contribute to the limited extant research on this topic and population of opioid users. 7. Validation of additional modifiable risk factors for overdose. We will also conduct exploratory analyses examining association of incident overdose with well-established, modifiable risk factors, considered as time-dependent covariates. Factors to be considered include: use of selected drugs with opioids; periods of abstinence (self-imposed or structural);^4, 5^ increases in opioid dose,[^6^](#_ENREF_165) in particular after a period of abstinence ≥2 days; and use of opioids from a new source[^3^](#_ENREF_54) or in a new location.[^7^](#_ENREF_162) While these relationships have been assessed in cross-sectional studies, our prospective data will allow us to assess the effects of both recent exposures as well as longer-term exposure patterns. 8. Treatment effects and depression. Treatment effects and depression will be addressed by examining both modification and mediation of the treatment effect on overdose events by depression, as measured by the Center for Epidemiologic Studies-Depression Scale (CES-D). Effect modification will be examined by comparing treatment effects according to baseline depression score. Mediation will be assessed by examining both steps in the indirect pathway (treatment🡪depression, and depression🡪OD/death, controlling for treatment and potential confounders of the mediator/outcome relationship). |
| Study Design: | We will enroll at least 60 opioid-dependent naloxone recipients with a prior opioid overdose who will be randomized to receive repeated doses of a 45-minute IMB (Informational-Motivational-Behavior) –based counseling session in overdose prevention versus treatment as usual (TAU, defined as information and referrals), and followed over 16 months with 4 counseling sessions at months 0 (enrollment), 4, 8, and 12 for the intervention arm. All participants will complete an opioid urine screen at all visits, a Computer Assisted Personal Interview (CAPI) at enrollment and months 4, 8, 12, and 16, and rapid HIV test (or CD4 & viral load test for positive participants) and rapid HCV test at screening and month 16. |
| Inclusion Criteria: | (1) Age 18-65 years;  (2) Current opioid dependence by SCID;  (3) Urine positive for opioids during screening, excluding prescribed agonist maintenance therapy;  (4) History of prior opioid overdose;  (5) Previously received take-home naloxone;  (6) No serious illnesses likely to progress clinically during trial;  (7) Able and willing to provide informed consent, provide locator information, communicate in English, adhere to visit schedule. |
| Exclusion Criteria: | (1) Suicidal ideation by SCID;  (2) Currently participating in another interventional research study that could possible impact the study’s outcomes of interest;  (3) Any condition that, in the Principal Investigator’s judgment, interferes with safe study participation or adherence to study procedures. |
| Study Procedures/ Frequency: | All subjects will complete the following study visits: screening, enrollment, study visits every 4 months for a total of 16 months.  **Screen visit:** informed consent will be obtained at the beginning of the screening visit. After consent is obtained and eligibility is determined, a locator form is completed and HIPAA form is signed for substance abuse record retrieval and review of medical/criminal records. Screening visit will also include a clinical evaluation (Structured Clinical Interview for DSM-IV [SCID] for opioid dependence and suicidal ideation), blood-borne virus testing (rapid HIV/hepatitis C serology [if no confirmed serostatus] +/- CD4+ t cells & HIV viral load), and a urine toxicology test with expanded opioids.  **Enrollment (month 0):** At the enrollment visit, participants will be randomized to receive the behavioral intervention (n=40) or TAU (n=20). **Randomization** will be 2:1 using permuted blocks of randomly selected sizes 3 and 6. Participants will provide a urine toxicology text, and will undergo the baseline CAPI followed by initial counseling visit. The next visit will be scheduled and participants will be compensated for their time.  **Every 4-month follow up visits:** participant will be seen every 4 months for CAPI, followed by counseling for the intervention arm; the control group will be offered referrals to local services. At months 4, 8 and 12 participants will provide a urine toxicology text, and will undergo the baseline CAPI followed by counseling for participants in the treatment arm.  At month 16, participants will complete activities listed for the monthly visits, in addition to completing the SCID and a blood-borne virus testing (rapid HIV/hepatitis C serology [if no confirmed serostatus] +/- CD4+ t cells & HIV viral load). Participants in the treatment arm will not receive counseling at month 16.  The CAPI, which is administered at enrollment and months 4, 8, 12, and 16 includes demographic information (enrollment only), drug use history (enrollment only), extensive opiate overdose questions, drug use and drug-related risk behaviors, partner-by-partner data on injection/substance use/HCV status, quality of life scale (EQ5-D), Center for Epidemiologic Studies Depression Rating Scale, and Severity of Dependence Scale and participant satisfaction with treatment. |
| Treatment Arm: | REBOOT participants will receive repeated doses of a 45-minute IMB (Informational-Motivational-Behavior) –based counseling session in overdose prevention. |
| Reference Arm: | Participants in the reference arm will receive treatment as usual (TAU), which consists of referrals to harm reduction and other substance use services. |
| Statistical Methods: | Specific Aim 1: To determine feasibility of a randomized trial with REBOOT, we will calculate screening and visit completion rates from the study database, with exact 95% confidence intervals (Cis), overall and by arm. Between-group differences will be assessed using Fisher’s exact and Wilcoxon ranksum tests. We will calculate Kaplan-Meier curves for time to dropout, by group, and test for differences using the log-rank test.  Specific Aim 2: To determine acceptability of REBOOT, we will calculate counseling completion rates from the study database by visit, and tabulate the proportions of active arm participants attending 0-4 counseling sessions. Via CAPI, we will inquire about participant satisfaction with the intervention and belief that it affected their drug use behaviors; responses will be presented as means, medians, or proportions, as appropriate, with 95% Cis.  Specific Aim 3: To evaluate the influence of egocentric social network characteristics on overdose events and naloxone use, we will use GEE Poisson models with robust standard errors to evaluate the association between network size, evaluated at baseline and each return visit, and numbers of experienced and witnessed overdose events in the same period; zero-inflated models will be used if needed. Results from this analysis will inform study design of a full efficacy trial and determine if randomization stratified by network size or targeted sampling strategies to ensure diversity in network size are needed. In addition, we will explore the influence of homophily and assortativity on experienced and witnessed overdose events using similar methods. Newman’s method will be used to calculate assortativity coefficients, a measure of the degree of demographic and risk behavior similarity within participants’ egocentric networks.  **Secondary analyses**: Exploratory analyses include preliminary efficacy estimates of REBOOT in decreasing overdose events (non-fatal or death), decreasing frequency of modifiable overdose / drug-related HIV risk behaviors, and increasing days of abstinence from illicit opioids and in substance abuse treatment.  Treatment effects on frequency of overdose events***.*** To determine if REBOOT, compared to TAU, reduces the risk of overdose among high-risk opioid users who have received take-home naloxone, as measured by the number of overdose events over 16 months. Overdose events will be determined by CAPI every 4 months via time-line follow-back of questions to determine the approximate date of non-fatal overdose that have proven reliable in multiple settings,^1-3^ with fatal episodes identified as above. We expect that repeated overdose events may be reasonably common in a subset of higher risk participants. To take advantage of this information, we will estimate treatment effects using Poisson models for the number of OD events in each reporting period, with robust standard errors to account for within-subject correlation and over-dispersion. |

This study will be conducted in accordance with the guidelines of Good Clinical Practices (GCPs) including archiving of essential documents.

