## Inclusion Criteria

Subjects must meet *all* of the following inclusion criteria to be eligible for participation in this study.

1. Age 18-65 years;
2. Current opioid dependence by SCID;
3. Urine positive for opioids during screening, excluding prescribed agonist maintenance therapy;

(4) History of prior opioid overdose;

(5) Previously received take-home naloxone;

(6) No serious illnesses likely to progress clinically during trial;

(7) Able and willing to provide informed consent, provide locator information, communicate in English, adhere to visit schedule.

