### 5.4.2. Computer Assisted Personal Interview (CAPI)

All participants will receive a CAPI at enrollment and months 4, 8, 12, and 16. The CAPI will **always** be conducted by a staffperson blinded to participant’s study arm and prior to administration of the REBOOT intervention or control arm procedures.

The CAPI includes demographic information (enrollment only), drug use history (enrollment only), extensive opiate overdose questions, drug use and drug-related risk behaviors, partner-by-partner data on injection/substance use/HCV status, quality of life scale (EQ5-D), Center for Epidemiologic Studies Depression Rating Scale, and Severity of Dependence Scale and participant satisfaction with treatment.

Primary and secondary outcome variables will be obtained from standardized scales assessed using CAPI to minimize underreporting of risk activities and enhance standardization.^4^ We will utilize the same overdose measures as in the pilot, which were developed in collaboration with other investigators (Drs [name], [name], [name], and [name]) to maximize comparability among overdose studies.

- **Quality of Life Surveys:** The quality of life scale included in this study is the EQ5-D. It will be completed by participants at enrollment and months 4, 8, 12 and 16 regardless of study arm. The Quality of Life Survey will be included in the CAPI.
- **Depression Rating Scale** The depression rating scale included in this study is the Center for Epidemiologic Studies Depression Rating Scale. It will be completed by participants at enrollment and months 4, 8, 12 and 16 regardless of study arm. The Depression Rating Scale will be included in the CAPI.
- **Severity of Dependence Scale:** The Severity of Dependence Scale will be completed by participants at enrollment and months 4, 8, 12 and 16 regardless of study arm. The Severity of Dependence Scale will be included in the CAPI.

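### The exploratory overdose-event model names no term for overdoses before enrollment; defining that count and adjusting for it is a nearly free improvement of uncertain size

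*Protocol*

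**What the plan says.** The Synopsis (Statistical Methods, treatment effects on frequency of overdose events) defines the outcome "as measured by the number of overdose events over 16 months". It introduces the model with an expectation about how events will be distributed: "We expect that repeated overdose events may be reasonably common in a subset of higher risk participants". The model follows: "To take advantage of this information, we will estimate treatment effects using Poisson models for the number of OD events in each reporting period". Its variance estimate is specified as well: "with robust standard errors to account for within-subject correlation and over-dispersion". No covariate is named. Section 8.4.2 (Exploratory Analyses) adds none.

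On baseline data, section 5.4.2 says "All participants will receive a CAPI at enrollment and months 4, 8, 12, and 16" and lists among the contents "extensive opiate overdose questions, drug use and drug-related risk behaviors". The interviewer is blinded to arm and the interview precedes counseling. Eligibility requires "History of prior opioid overdose", without a time window.

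The Enrollment Visit section sets randomization at 2:1 (40 and 20) in permuted blocks of 3 and 6, and names no stratification factor. Section 8.5 (Sample Size) declares precision and power for efficacy low, and says the exploratory results will be read cautiously in designing the full-scale trial.

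**The concern.** The protocol chooses a count model because it expects some participants to overdose repeatedly. By the same reasoning, a participant's recent overdose count should help explain the later count, but the model as stated does not use it. Robust standard errors make the interval honest about over-dispersion and within-subject correlation. They do not recover precision, and they do not correct the estimate when frequent overdosers happen to fall more in one arm.

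With 20 controls and no stratification, a few such participants can move the rate ratio noticeably. At stake is the width and stability of an interval that will help design the next trial.

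**Working it through.** **1. The protocol's own precision figures.** Section 8.5 gives 95% half-widths for means of 0.32 SD (active arm) and 0.26 SD (overall). With t(0.975, n-1)/sqrt(n): n = 40 gives 0.320 and n = 60 gives 0.258. Both reproduce. Neither depends on the overdose model, and no rate, effect size or power is stated for the overdose comparison. The point therefore changes no stated figure.

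**2. Is a baseline count available?** The overdose questions are in the interview, and the interview is given at enrollment. Aim 3 relates network size at baseline and at each return visit to overdose counts for the matching period, which needs a count for the baseline period. Section 5.4.3 takes treatment records from 4 months before enrollment. A pre-enrollment count is very probably collected, but no look-back window for overdoses is defined. Since every participant has a prior overdose, a yes/no history would not discriminate; a count within a window is needed.

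**3. Chance imbalance.** The SE of a standardized baseline difference is sqrt(1/40 + 1/20) = 0.274. The chance of an imbalance above 0.3 SD in either direction is 2 × (1 - Phi(0.3/0.274)) = 0.27. This normal approximation holds for any baseline variable at this split and is not specific to overdose counts.

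**4. Gain from adjustment.** Simulated trials of 40 v 20 used gamma-frailty Poisson counts, a 4-month baseline and 16 months of follow-up. Poisson regression with robust SE was fitted with and without log(1 + baseline count), 1,500 runs per setting. All of these inputs are assumed: 0.15-0.6 overdoses per 4 months, frailty variance 1-4, and the share of participants whose risk level persists into follow-up. Each cell gives the SD of the log rate ratio, adjusted over unadjusted, for full / half / no persistence (no treatment effect):

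| Rate per 4 months | Variance 1 | Variance 2 | Variance 4 |
| --- | --- | --- | --- |
| 0.15 | 0.98 / 1.01 / 1.01 | 0.95 / 1.00 / 1.01 | 0.92 / 0.97 / 1.01 |
| 0.3 | 0.95 / 1.00 / 1.00 | 0.89 / 0.98 / 1.01 | 0.82 / 0.97 / 1.00 |
| 0.6 | 0.89 / 0.97 / 1.01 | 0.79 / 0.95 / 1.01 | 0.68 / 0.92 / 1.02 |

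For a true rate ratio of 0.5 and full persistence, power goes from 32% to 33% (rate 0.15, variance 1), from 34% to 41% (0.3, variance 2) and from 27% to 50% (0.6, variance 4). With half persistence the gain is 0-6 points. Rejection under no effect is about 6-11% with and without adjustment, so adjustment neither causes nor cures that small-sample excess.

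A separate simulation with log(baseline count + 0.5) gave variance ratios at rate 0.3 of 0.79 (variance 2) and 0.90 (variance 1). These match the full-persistence cells (0.89² = 0.79; 0.95² = 0.90), so the added constant matters little there.

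**5. Could the baseline period already be in the model?** The abstinence and treatment-day objectives refer to five periods of 4 months, while 16 months of follow-up holds 16/4 = 4. The fifth is presumably pre-enrollment. If the overdose model also took that period as an outcome row, with no arm-by-period term, the arm effect would average in events from before treatment. With equal rates before treatment and a true rate ratio of 0.5, the estimate would be near (1 + 4 × 0.5)/5 = 0.60.

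**The case against.** The strongest reply is that silence is not an error. The protocol names no covariates for this model but excludes none, and a covariate list for an exploratory model is often left to the SAP, which was not available here. A reader might infer that the plan commits to a comparison by arm alone; the text does not say so. What remains is that the protocol itself fixes the model family, outcome unit and variance method. It also names model terms elsewhere, such as network size, time-dependent risk factors and baseline depression score. A better choice can fairly be recommended at this point.

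A reader might also infer that the efficacy estimate is biased or invalid. It is not: randomization protects the unadjusted comparison, and its standard error already reflects chance imbalance.

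Nor do the documents support calling the prior count the strongest predictor, or treating a 4-month overdose count as an established data item. Both are inferences. Persistence of risk is also open to doubt, since an overdose may change behavior, so a range showing only gains would be selective.

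Finally, the five-period wording suggests that the abstinence and treatment-day models may already hold the baseline period as a response. That objection stands against applying the same covariate to every outcome. It does not remove the point for the overdose model, whose outcome is defined over 16 months and which, on the five-period reading, would have the dilution shown above.

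**Conclusion.** The point holds as a recommendation to improve an exploratory analysis, not as a flaw that undermines it. The overdose model as written does not use a baseline measure that is very probably in hand, in a small, unstratified 2:1 trial where events are expected to concentrate in some participants.

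The benefit lies between a reduction of about a third in the SD of the log rate ratio (ratio 0.68: high rate, strong clustering, fully persistent risk) and none, with a loss of at most about 2% (ratio 1.02). Where it falls depends on rates, clustering and persistence that the protocol does not give. The primary aims and the stated precision figures are unaffected.

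**What to change.** For the overdose-event model:

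- Define the pre-enrollment overdose count and its look-back window from the enrollment interview.
- State that outcome rows are the four post-randomization periods only.
- Add log(baseline count + 0.5) as a covariate, and report the unadjusted estimate beside the adjusted one.

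For the other repeated outcomes (co-use frequency, RAB score), use the enrollment value as a covariate only where the baseline period is not also an outcome row. For the abstinence and treatment-day models, first reconcile the five reporting periods with 16 months of follow-up, so that the baseline value enters once only.

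The cost is a few sentences and one degree of freedom per model. No new data are needed if the enrollment interview yields a count within a defined window, which should be confirmed against the questionnaire.

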# OBJECTIVES

The primary objectives of this study are:

- To determine the feasibility of a randomized trial with REBOOT.
- To determine acceptability of REBOOT.
- To evaluate the influence of egocentric social network characteristics on overdose events and naloxone use.

Exploratory objectives of this study are:

- To determine the preliminary efficacy estimates of REBOOT in decreasing overdose events (non-fatal or death), decreasing frequency of modifiable overdose / drug-related HIV risk behaviors, and increasing days of abstinence from illicit opioids and in substance use treatment.
- To provide a preliminary estimate of the effect of REBOOT, compared to TAU, on overdose risk behaviors, as measured by frequency of using opioids with alcohol, cocaine, or benzodiazepines (the most common modifiable overdose risk behavior), we will use GEE Poisson models with robust standard errors to assess reductions in overdose risks and linear mixed models to assess effects on the RAB scale.
- To provide a preliminary estimate of the effect of REBOOT, compared to TAU, on HIV risk behaviors among high-risk opioid users who have received take-home naloxone, as measured by frequency of using opioids with alcohol, cocaine, or benzodiazepines (the most common modifiable overdose risk behavior); and the HIV Risk Assessment Battery (RAB) drug-related risk scale score over 16 months. We will use GEE Poisson models with robust standard errors to assess reductions in overdose risks and linear mixed models to assess effects on the RAB scale.
- We will use GEE Poisson models with robust standard errors to assess evidence that the intervention increases days of abstinence from illicit opioids and days of drug treatment within each of five 4-month reporting periods.
- We will use GEE Poisson models with robust standard errors to assess evidence that the intervention increases the use of naloxone during overdose events witnessed by participants.

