### Enrollment Visit

Enrollment tests and procedures will be completed prior to enrollment and receipt of the first counseling session.

On the enrollment visit, participants will be randomized to receive the behavioral intervention (n=40) or TAU (n=20). **Randomization** will be 2:1 using permuted blocks of randomly selected sizes 3 and 6.

Participants will provide a urine toxicology test, and will undergo the baseline CAPI followed by initial counseling for the treatment group and TAU for the reference group. The next visit will be scheduled and participants will be compensated for their time.

Subjects will be compensated $30 for the enrollment visit.

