## Data Analysis

### Primary Analysis

Specific Aim 1: To determine feasibility of a randomized trial with REBOOT, we will calculate screening and visit completion rates from the study database, with exact 95% confidence intervals (Cis), overall and by arm. Between-group differences will be assessed using Fisher’s exact and Wilcoxon ranksum tests. We will calculate Kaplan-Meier curves for time to dropout, by group, and test for differences using the log-rank test.

Specific Aim 2: To determine acceptability of REBOOT, we will calculate counseling completion rates from the study database by visit, and tabulate the proportions of active arm participants attending 0-4 counseling sessions. Via CAPI, we will inquire about participant satisfaction with the intervention and belief that it affected their drug use behaviors; responses will be presented as means, medians, or proportions, as appropriate, with 95% Cis.

Specific Aim 3: To evaluate the influence of egocentric social network characteristics on overdose events and naloxone use, we will use GEE Poisson models with robust standard errors to evaluate the association between network size, evaluated at baseline and each return visit, and numbers of experienced and witnessed overdose events in the same period; zero-inflated models will be used if needed. Results from this analysis will inform study design of a full efficacy trial and determine if randomization stratified by network size or targeted sampling strategies to ensure diversity in network size are needed. In addition, we will explore the influence of homophily and assortativity on experienced and witnessed overdose events using similar methods. Newman’s method will be used to calculate assortativity coefficients, a measure of the degree of demographic and risk behavior similarity within participants’ egocentric networks.

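### The Poisson model for overdose counts reported at visits is not protected against dropout that follows earlier overdoses differently by arm; using the baseline count and one sensitivity model would limit the bias

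*Protocol*

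**What the plan says.** The Protocol Synopsis, Statistical Methods, describes the overdose analysis: "we will estimate treatment effects using Poisson models for the number of OD events in each reporting period, with robust standard errors". It gives these standard errors one purpose: "with robust standard errors to account for within-subject correlation and over-dispersion". Dates of non-fatal overdoses come from the CAPI every four months. The same paragraph anticipates that some high-risk participants will overdose more than once.

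Section 8.4.1 (Specific Aim 1) compares loss to follow-up between arms through "Kaplan-Meier curves for time to dropout, by group" and a log-rank test. This is a feasibility result, and no stated efficacy analysis uses it.

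Section 5.4.3 takes deaths from vital records and locator contacts, and substance use treatment data from administrative records. Neither depends on attending visits. Section 8.5 calls the efficacy analyses exploratory, with low precision and power. It says their results will be read cautiously when the full-scale trial is designed.

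**The concern.** A Poisson model fitted to the reported periods, with correlation handled only through the standard errors, estimates the rate among periods that were observed. If people with frequent overdoses leave, the observed periods come increasingly from people with few overdoses. If that happens to the same degree in both arms, the effect nearly cancels in the ratio. If it happens more under TAU, the TAU rate is understated and a real benefit shrinks. If it happens more under REBOOT, the benefit is exaggerated. The reported confidence interval shows neither. Since these estimates feed into the design of the full trial, a cheap safeguard is worthwhile.

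**Working it through.** **The plan's own figures.** The protocol gives no overdose rate, dropout rate or target rate ratio, so none can be reproduced on this point. Its only numbers are the precision figures in Section 8.5, and they reproduce. For means, t(0.975, n-1)/√n gives 0.320 SD at n=40 and 0.258 SD at n=60. For proportions of 0.1 to 0.5, 1.96·√(p(1-p)/n) gives 9.3-15.5 and 7.6-12.7 percentage points.

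**Inputs.**
- From the protocol: 2:1 allocation (40 v 20), four 4-month follow-up periods, overdose questions in the enrollment CAPI.
- Assumed: true rate ratio 0.70; mean 0.25 overdoses per period; between-person variance v of 1 or 2 times the squared mean (gamma or lognormal); 5% dropout per visit without an overdose in the previous period; 25% after one under TAU and 5-10% under REBOOT. This implies about 30% dropout by month 16 under TAU and 20% under REBOOT.

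**One visit by hand (gamma, v=1, REBOOT 10%).**
1. No overdose in the baseline period: probability 1/(1+0.25) = 0.80. Expected next-period rate in this group at the TAU level: 0.25/1.25 = 0.20.
2. At least one overdose: probability 0.20. Rate (0.25 - 0.80×0.20)/0.20 = 0.45.
3. TAU rate among those still seen: (0.80×0.95×0.20 + 0.20×0.75×0.45)/(0.76 + 0.15) = 0.2195/0.91 = 0.241.
4. REBOOT: 0.70 × (0.152 + 0.20×0.90×0.45)/(0.76 + 0.18) = 0.70 × 0.233/0.94 = 0.174.
5. Ratio 0.174/0.241 = 0.72 after a single round of dropout. With 25% in both arms the selection is identical at this visit and the ratio is exactly 0.70.

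**All four visits, large-sample simulation.**

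| Analysis | Dropout after overdose | Limit (true 0.70) |
| --- | --- | --- |
| Poisson, independence | TAU 25%, REBOOT 5-10% | 0.74-0.80 |
| Poisson, independence | TAU 5%, REBOOT 25% | 0.61-0.66 |
| Poisson, independence | 25% in both | 0.70-0.72 |
| Poisson, adjusted for baseline count | TAU 25%, REBOOT 5-10% | 0.71-0.74 |
| Exchangeable GEE, follow-up rows only | TAU 25%, REBOOT 5-10% | 0.72-0.76 |
| Exchangeable GEE with baseline row (gamma only) | TAU 25%, REBOOT 5-10% | 0.705-0.716 |
| Frailty likelihood, baseline row and period term | TAU 25%, REBOOT 5-10% | 0.695-0.704 |

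Without within-person clustering there is no bias.

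**Against sampling error.** The largest shifts are ln(0.80/0.70) = 0.13 and ln(0.61/0.70) = -0.14. With 40 v 20 and an assumed 0.3 overdoses per period, the standard error of the log rate ratio is about 0.37-0.54. The 95% interval then spans a factor of exp(1.96×0.37) = 2.1 to exp(1.96×0.54) = 2.9 either way. The largest bias is 0.14/0.54 = 0.26 to 0.14/0.37 = 0.38 of one standard error.

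**The period term.** If overdoses fall by 30% in both arms after enrollment, a baseline-row model without a period effect converges to about 0.53 instead of 0.70. It credits the common decline to REBOOT. With the term included, the root mean squared error of the log rate ratio at 40 v 20 moves only from 0.47-0.62 (planned model) to 0.45-0.56.

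**The case against.** The strongest reply is that a marginal model with robust standard errors is a standard choice. Working correlation, weights and missing-data assumptions commonly belong in the SAP, which was not available here. That stands in part. The protocol's silence on weights is no fault, and a GEE with exchangeable correlation and a baseline row leaves only about 1-2% bias. But for overdose the stated text names a Poisson model with correlation handled through the standard errors, and that estimator is exposed.

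It is also fair that the scenario is assumed. Comparing dropout by arm under Aim 1 does not mean that the protocol expects a difference.

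Three stronger readings are tempting and are not supported:
- A reader might infer that the RAB score is better protected because it gets "linear mixed models to assess effects on the RAB scale". Such a model tolerates dropout explained by earlier RAB scores, not dropout driven by overdoses, which lie outside it. In a check with a score of SD about 4.2, overdose-driven dropout still biased it by -0.06 to -0.18.
- A reader might extend the point to every count outcome. Deaths and treatment days come from records. Abstinence days are bounded by the period length, and naloxone use occurs only within witnessed overdoses. Both need a different likelihood, and neither was checked.
- A reader might expect a large precision gain from the baseline-row model. That appears only when the period effect is left out, which is unsafe.

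**Conclusion.** The point holds for overdose counts reported at visits. The stated Poisson model is biased when overdoses cluster within persons and dropout after an overdose differs by arm. Under the assumed rates the limit is about 0.74-0.80, or 0.61-0.66 with the pattern reversed, against a true 0.70. If dropout after overdose is the same in both arms, the bias is close to nil. The protocol supplies none of these rates, so the figures show what could happen, not what to expect. In a pilot of this size the bias is well below sampling error. This is a low-cost improvement and does not invalidate the planned analysis.

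**What to change.** 1. Keep the planned Poisson estimate for overdose counts, and adjust it for the baseline-period count from the enrollment CAPI. First confirm that those questions cover the four months before enrollment, or use an offset for their actual length. The Objectives refer to five reporting periods of four months for abstinence and treatment days. Follow-up has four, which suggests that a baseline period was intended.
2. Pre-specify one sensitivity analysis: a random-intercept Poisson or negative binomial model fitted by maximum likelihood. Include the baseline period as an outcome row, a post-baseline period effect common to both arms, and an arm effect that starts after randomization. The period effect is essential. With a log link and a random intercept the arm effect remains a rate ratio.
3. Report both estimates whatever the Aim 1 dropout comparison shows. That test has little power at 40 v 20 and should not choose the model.
4. Limit this to overdose counts reported at visits.

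Cost: one more model, in the Stata software already named, on data already collected. The downside is reliance on an assumed random-effect distribution, although fitting a gamma to lognormal heterogeneity caused no visible bias in the check. The precision gain is modest.
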